## Abstract

Non-adherence to immunosuppressive medication after kidney transplant is an important cause of graft rejection and loss. Approaches to minimization of non-adherence have focused on the identification of episodes of medication non-adherence, but by then irreparable harm to the graft may already have occurred, and a more effective approach would be to adopt preventive measures in patients who may have difficulty in adhering to medication. The aim of this study protocol is to develop and validate a clinical questionnaire for assessing, in kidney transplant candidate patients in the pre-transplant setting, the predisposition to non-adherence to immunosuppressive medication. In this multicenter, prospective study, a pilot questionnaire in Brazilian Portuguese language, composed of Likert-scaled statements expressing patients’ beliefs, behaviors and barriers regarding medication taking will be assembled from a literature review, from focus groups, and an expert panel. The pilot questionnaire will be administered to a minimum of 300 patients in kidney transplant waiting lists and exploratory factor analysis will be used for development of the definitive questionnaire. A random subsample of a minimum of 60 patients will have the scale re-administered after one month for evaluation of test-retest reliability. A multicenter, external validation study will include 364 kidney transplant candidates who will be evaluated immediately before surgery and at months 3, 6 and 12 post-transplant for assessment of concurrent validity, by comparison with two scales that assess medication non-adherence, and for determination of predictive validity using a triangulation method for assessment of medication non-adherence. Structural validity will be assessed with confirmatory factor analysis using structural equation modeling. Cross-cultural generalizability and validity will be assessed by a multicenter study, in which a translation of the scale to another language will be administered to kidney transplant candidate patients from a different culture, with a subsample being selected for test-retest. This study will be conducted in Spain with a Spanish translation of the scale.

## Introduction

Chronic Kidney Disease (CKD) was defined by the National Kidney Foundation, in its document Kidney Disease Outcomes Quality Initiative, as kidney damage present for a period equal to or greater than three months, characterized by structural or functional abnormalities of the kidney, with or without a decrease in the glomerular filtration rate, manifested by histopathological abnormalities or markers of kidney damage, including blood or urinary changes, or in imaging tests [1]. CKD is an important medical and public health problem, and its prevalence is increasing worldwide [2, 3]. It is estimated that more than 10% of the global population suffers from CKD [4]. In Brazil, according to the 2016 census of the Brazilian Society of Nephrology, it is estimated that there are 122,825 patients in dialysis programs with CKD in its most advanced stage [5]. This number represents an increase of 31,500 patients in the last 5 years (91,314 in 2011) [5].

Renal replacement therapies such as hemodialysis, peritoneal dialysis and kidney transplantation are forms of treatment for patients with stage 5 CKD, in the functional failure stage [3, 6]. Kidney Transplantation is currently considered the best therapeutic option for patients with CKD in its most advanced stage, both from medical, social and economic point of views [7–9]. It increases quality-adjusted life years by five times and is more cost-effective when compared to dialysis.

Although superior to dialysis treatment, kidney transplantation involves the inherent risk of rejection and/or graft failure that incurs costly hospitalizations, laboratory tests and anti-rejection treatments that are associated with poor patient outcomes [3, 10–14]. To minimize the risk of rejection, recipient patients are placed on lifelong regimens of immunosuppressive drug treatments [15] and are monitored for signs of rejection [3]. A combination of two or three different immunosuppressants are taken on a long-term basis to prevent rejection. However, as with all medications, patients may experience adverse reactions and these may include an increased risk of infections, diabetes, increased susceptibility to certain cancers, increased blood pressure and weight gain [12]. It is also true that the immunosuppression process can increase the risk of comorbidities. Despite the nuances of the medication, adherence to the immunosuppressant regimen is vital to providing the grafted kidney with the best chance of survival and function after kidney transplantation [6]. Graft survival after kidney transplantation emphasizes adherence to immunosuppressive therapy, [11, 12, 16] as well as adherence to other prescribed medications, which are important to ensure control of the comorbidities that commonly accompany patients with end-stage CKD and thus not compromising the health of the patient and the transplanted kidney [7].

However, despite a long and frustrating time on the waiting list following a successful transplant, many patients develop problems with adherence to their immunosuppressive medications [7, 16]. Not taking prescribed immunosuppressive drugs (defined as taking drugs <95.1% of days) is associated with a 60% increased risk of kidney transplant failure and premature death [11, 17]. Adherence in this context refers to the “extent to which the patient’s behavior matches agreed prescriber recommendations” [6], and non-adherence (NA) as “deviation from the prescribed drug regimen sufficient to negatively influence the effect” [18]. In a broader context, adherence is defined by the World Health Organization as “the extent to which a person’s behavior–taking medication, following a diet and/or carrying out lifestyle changes–corresponds to the agreed recommendations of a health professional” [19]. Non-adherence to immunosuppressive medication is an important risk factor for unfavorable post-transplant clinical outcomes, reducing patient survival and causing waste of health resources [20]. However, it remains a common problem in this patient population and has been identified as the second common cause of late graft failure in kidney transplant patients. In 2011, Suárez et al. [21] estimated that the non-adherence rate is between 20% and 54% and that the lack of compliance can contribute to 20% and 16% of graft loss. A recent meta-analysis revealed that the magnitude of NA for immunosuppressants in kidney transplant recipients was as high as 35.6 cases per 100 patient-years. The incidence of NA among kidney transplant recipients was significantly higher than that of the general population of solid organ transplant recipients, which was 22.6 cases per 100 patient-years. That study estimated that 15% to 60% of late acute rejections and 5% to 36% of graft losses were associated with NA in kidney transplant patients [18, 22].

The World Health Organization categorizes non-adherence as a multidimensional phenomenon, determined by 5 factors: economic and structural, complexity of the therapeutic regimen, satisfaction with care, standard of care and patient factors [19, 23]. Within patient factors, the literature has mentioned that adherence is associated with 3 dimensions: behavior, beliefs and barriers. Thus, there is a need for easy-to-use scales that correctly measure the 3 dimensions associated with medication use that influence adherence: medication-taking behavior, barriers to adherence, and patients’ beliefs about medication.

A 2013 systematic review of adherence scales evaluated sixty articles that described or evaluated 43 scales [24]. These scales included items that elucidated information about the patient’s medication-taking behavior and/or attempts to identify barriers to good medication-taking behavior or beliefs associated with adherence, and were categorized into five groups based on the information they were intended to elucidate. Each group had 2 to 3 scales considered the most representative based on the number of correlated and developmental studies. The scales in group 1 encompassed information only on medication-taking behavior, in which the MARS-5 scale was the highlight, consisting of only 5 questions and scored on the Likert scale; the scales of group 2 sought information on medication-taking behavior and barriers to adherence, and the most representative were the ASK-20 (Adherence Starts with Knowledge-20), which is a scale consisting of 20 questions validated in patients with asthma, diabetes or depression, the RAM (Reported Adherence to Medicine), which assesses beliefs about medicines for general and personal use and was validated with patients with chronic diseases (asthmatic, diabetic, psychiatric and undergoing dialysis) and the MMAS (Morisky Medication Adherence Scale) which examines the psychometric properties in patients with hypertension, consisting of 8 questions; the scales of group 3 assess adherence barriers and the most representative was the MAQ (Medication Adherence Questionnaire); group 4 seeks information only on beliefs associated with adherence and is represented by the RAM (Reported Adherence to Medicine); those in group 5 look for information about barriers and beliefs associated with adherence, they are: CQR (Compliance Questionnaire Rheumatology) and MARS.

All scales identified in this systematic review were intended to identify patients who, retrospectively, show insufficient adherence to treatment. There has been a large effort in the search for risk factors of NA in kidney transplant patients but, surprisingly, such efforts have not been followed by attempts to develop instruments for assessing the risk of NA in kidney pre-transplant patients. To the best of our knowledge, only two NA risk stratification tools have been published [25, 26] but intended to be applied only after transplant. Given the high number of kidney transplants performed, the great importance of adherence by patients with immunosuppressants after kidney transplantation in the results of kidney transplantation, the high cost for the health system with anti-rejection treatment with risk, including, of returning to hemodialysis and, as a last resort, a retransplantation, and the lack of a clinical questionnaire that assesses the predisposition to adherence to immunosuppressants to be applied in kidney pre-transplantation patients, it is clear that this community needs effective tools to identify patients at risk for NA, before undergoing kidney transplantation, so that actions can be taken to monitor the treatment, prevent non-adherence and motivate the patient to reduce the risk of adverse outcomes arising from non-adherence. In clinical practice, such tool could be used for assessment of medication adherence of kidney transplant candidates in the pre-transplantation setting, which, in combination with an evaluation of risk factors of NA and adherence barriers, could guide personalized adherence plans including appropriate education, counseling and post-transplant surveillance. In clinical research, that tool could be useful in the evaluation of interventions directed to improving patients’ beliefs and behaviors towards medication, and in the selection of prescription-complying patients for inclusion in randomized clinical trials of immunosuppressants.

The Kidney AlloTransplant Immunosuppressant Therapy Adherence (KATITA) project was set up to address the unmet medical need for a tool assessing the predisposition to immunosuppressant medication non-adherence of kidney transplant candidate patients, in the pre-transplant setting. The project aims at the full development of a validated KATITA scale and is divided into four sequential phases: development of a psychometric scale, internal validation study, external validation study, and validation study of a cross-cultural adaptation to a different language.

## Materials and methods

### Objectives

The objectives of each project phase are as follows: First phase, development of a psychometric scale: 1) to develop a comprehensive item pool for KATITA; 2) to identify the psychometric dimensions of medication non-adherence in the pre-transplant setting; 3) to select the relevant items composing the final KATITA questionnaire. Second phase, internal validation study: 1) to evaluate internal consistency reliability of KATITA; 2) to evaluate test-retest reliability of KATITA; 3) to evaluate construct validity by assessing convergent validity. Third phase, external validation study: 1) to evaluate criterion validity by assessing concurrent validity and predictive validity; 2) to evaluate the scale structural validity. Fourth phase, transcultural adaptation to a different language: 1) to translate KATITA to a different language using the translation-back translation method; 2) to evaluate reliability of the KATITA translation using internal consistency and test-retest reliability methods.

The study protocol was approved by the Research Ethics Committee of the coordinating center at Hospital Universitario Onofre Lopes in Natal-RN, Brazil (authorization number 3.179.920 of March 1, 2019). All four study phases are considered minimal risk research, no experimental interventions will be performed on patients, and no additional data will be collected beyond the necessary for usual routine care. Approval will be obtained from the Institutional Review Boards of every collaborating center and signed informed consent will be obtained from all participating patients.

### Scale development

A flowchart of the scale development process is shown in Fig 1, illustrating the steps of the scale development process, the objectives of each step, and the sample size planned for each step.

**Fig 1 pone.0305953.g001:**
[figure not shown]
Flowchart of the scale development process. The chief steps are shown in boxes, with arrows pointing to the main objectives of each step.

#### Item pool development

Once the construct is clearly identified, based on the definitions of medication non-adherence presented above, the first step in scale development will be item generation, the identification of the appropriate questionnaire questions, which will combine a deductive and an inductive method. The former will consist of a search for medication adherence scales from bibliographic databases. Statements from those scales related to patients’ medication-taking behaviors, to barriers to good medication-taking behavior, or to beliefs associated with medication adherence will be selected for inclusion in a preliminary item pool of potential statements for the KATITA scale. The inductive method will consist of a focus group of consecutive patients attending the nephrology clinic of the coordinating center, of both sexes, over 18-years-old, who are in the kidney transplant waiting list, moderated by a psychologist experienced in kidney transplant patients. The patients will be asked to review and reformulate or rephrase the previous selected items, and add new ones reflecting their experiences and thoughts on medication taking. The focus group sessions duration should not exceed 60 minutes and will be repeated until saturation occurs, that is, when no additional concepts are elicited in two consecutive sessions. The focus group sessions will be recorded and the transcripts will be reviewed by the study investigators, who will select all the statements that may reflect patients’ attitudes, behaviors, beliefs and barriers to medication adherence.

The next task will be the assessment of content validity by a panel of three clinical pharmacists with extensive experience in the pharmaceutical care of kidney transplant patients. These expert judges, based on their experience in interactions with this population during pharmacotherapeutic consultations, will independently review each item to decide, through consensus, whether it should be eliminated due to irrelevancy or unrelatedness to medication non-adherence. The panel will also review the wording of each item for complexity and ambiguity, and may generate new questionnaire items.

The resulting item pool will be submitted to cognitive interviews with a small sample of patients selected with the same criteria as those of the focus groups but who had not participated in the focus group, to determine whether the intended meaning of each item is fully perceived by the respondents. In this process, patients will respond to each item and then asked to explain why they responded that way [27]. This process will culminate in a set of items that will be used for the construction of the KATITA questionnaire through the statistical analysis of the responses of a random sample of target subjects to each item.

#### Pilot questionnaire administration

Thirteen healthcare centers in three capitals of northeastern Brazil states, of which seven are hemodialysis centers and six are tertiary care hospitals performing kidney transplant, will be included and will enroll consecutive patients over 18 years of age, of both sexes, who are in waiting lists for kidney transplant and are able to read and communicate, excluding patients who are candidates for kidney retransplant. The patients will be asked to self-rate each item in a 5-point Likert scale, according to their level of agreement with the presented statement, from 0 (strongly disagree) to 4 (strongly agree). Demographic data will be collected (age, sex, ethnicity, level of education, social support), as well as clinical data related to kidney disease (current dialysis, time on dialysis, etiology of kidney disease and number of blood transfusions). A subsample of the patients will be asked to repeat the administration of the questionnaire after six weeks for assessment of the scale temporal stability through test-retest analysis. These will be consecutive patients who had responded to the questionnaire.

#### Factor analysis

The collected data will be analyzed by exploratory factor analysis for factor extraction and subsequent item selection, a process that will result in the final KATITA questionnaire. Fig 2 shows the steps required for the development of the final KATITA questionnaire from the data collected with the pilot questionnaire. Factor analysis is a statistical method widely used for the discovery of unobserved variables, which are called factors, that determined the expression of a set of variables that can be measured. These hidden factors represent dimensions, or facets, of the construct of interest and the meanings of the factors are defined by the investigator, guided by the pattern of relationships between the observed variables and each factor. Factor analysis fits as many factors as there are items in a questionnaire to the empirically obtained dataset, and two important statistics are computed, the factor loadings and the eigenvalues. The former represent the correlation between a questionnaire item and a factor, the latter a measure of the variance in all questionnaire items that is explained by a factor. These statistics will help refining the questionnaire. The eigenvalues are used to select which factors have a significant correlation with the construct of interest, by retaining only those factors with an eigenvalue greater than 1, the so-called Kaiser criterion.

**Fig 2 pone.0305953.g002:**
[figure not shown]
Overview of the steps required for development of the KATITA scale from data obtained with the pilot questionnaire.

As the dimensions are then reduced to a small number of factors, a better fit to the data can be achieved by positioning only the few retained factors and disregarding the remaining. This is called factor rotation and usually results in higher factor loadings of those items that loaded high on a factor, while those that loaded low will then have loads near zero. The new factor loadings are then used to select the items that are significantly correlated with each factor, retaining only the items with factor loadings above a certain value. This procedure usually causes each item to be associated to at most one factor, making it easier to understand which facet of the construct each factor is measuring. Factor rotation can be orthogonal or oblique, depending on whether the factors are constrained to be at right angles of each other, or free to be placed at the angles that provide the best fit to the data. Although an orthogonal rotation may not fit the data as closely as an oblique rotation, it has the advantage that the factors remain uncorrelated and, therefore, a global scale score can be obtained from the sum of subscale scores, which is not possible after an oblique rotation.

Before proceeding to reliability and internal validity evaluation, item analysis will be conducted to refine the questionnaire. Irrelevant and redundant items do inflate statistics of reliability and therefore should be removed from the questionnaire according to the extent of observed correlations of each item with other items in the scale and with the scale scores [28].

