### Questionnaire development

Exploratory factor analysis will be used for questionnaire development. Only those factors with an eigenvalue greater than 1, that is, factors that explain the variability in the scale more than a single item (Kaiser criterion), will be retained. If factor rotation is considered necessary to improve item selection, a varimax rotation, which is an orthogonal rotation, will be applied. Factor loadings less than 0.40 will be ignored. Items presenting a commonality significantly lower than the value observed for the remaining items will also be discarded. Pearson’s correlation will be used for item analysis and the following rules will be adopted for item reduction: inter-item correlations should not be greater than 0.70, which may indicate redundancy, neither less than 0.30, which suggests the item is measuring something different; item-test correlation, the correlation of each item with the scale score, should be high (>0.30), otherwise the item is probably measuring something different; item-rest correlation, the correlation of each item with the score formed with the remaining items, should be moderately low (between 0.30 and 0.70), otherwise the item may be redundant [28]. If a multidimensional scale is obtained, the item-to-own dimension correlation, the correlation of each item with the total score of its own subscale, should be high (>0.30). The assumption of independence of the factors will be tested with an inter-dimension correlation matrix and will be discarded if correlations are moderately high (>0.60).

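### Varimax is justified by the incorrect premise that a total score is impossible after oblique rotation, and eigenvalue >1, the only rule for the number of factors, is unreliable at N=300

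*Protocol article*

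**What the plan says.** - **Reason for orthogonal rotation** (Scale development, Factor analysis, text after the Fig 2 caption). The article concedes a cost and names one benefit: "Although an orthogonal rotation may not fit the data as closely as an oblique rotation, it has the advantage that the factors remain uncorrelated", so that "a global scale score can be obtained from the sum of subscale scores, which is not possible after an oblique rotation". No other reason is given.
- **Rotation chosen** (Statistical analysis, Questionnaire development): "If factor rotation is considered necessary to improve item selection, a varimax rotation, which is an orthogonal rotation, will be applied". No oblique rotation is named.
- **Check on independence** (same section): an inter-dimension correlation matrix is examined, and the independence assumption "will be discarded if correlations are moderately high (>0.60".
- **Number of factors.** Factor analysis selects factors "by retaining only those factors with an eigenvalue greater than 1, the so-called Kaiser criterion", and Questionnaire development repeats it: "Only those factors with an eigenvalue greater than 1". No second criterion is named. Neither the extraction method nor the number of pilot items is fixed.
- **Item selection** (Questionnaire development): "Factor loadings less than 0.40 will be ignored".
- **Use of the score.** Internal validity assessment computes Cronbach's alpha for the full scale as well as for each dimension. External validity assessment uses KATITA scores for change, concurrent validity and AUROC.

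**The concern.** The two points are separate.

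**Rotation.** The plan accepts a poorer fit in return for a benefit that does not exist. A summed score is a function of the item responses, and no rotation changes those. What supports reading a total as one predisposition is shared variance between subscales, which an orthogonal model sets to zero. The Introduction links adherence to behavior, beliefs and barriers, and the Factor analysis section calls factors facets of one construct. Correlated factors are therefore plausible, although the article does not state that they are expected. The 0.60 check is the only protection, and its limit is high.

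**Number of factors.** The retained factors decide which loadings are inspected, and so which items enter the instrument used in every later phase. A rule that can keep too many or too few factors, depending on unstated choices, is a weak basis for that step.

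**Working it through.** The article gives no figure here to reproduce. The development sample (at least 300), the 5-point items, the 0.60 limit and the eigenvalue rule come from the article. Item counts, loadings and factor correlations are assumptions.

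**1. A total exists after any rotation.** The total is T = Σ(item scores). Rotation replaces the loading matrix by an equivalent one and leaves the items unchanged, so T is the same number under varimax, promax or no rotation. Grouping items into subscales does not change T either, provided the same items are kept.

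**2. What supports the total.** Take 3 factors with m items each, equal loading l and factor correlation φ. Items correlate l² within a factor and l²φ across factors. The variance of the total is V = 3m + 3m(m−1)l² + 6m²l²φ. The share of V due to a common factor is (3ml)²φ / V. With m = 5 and l = 0.6:

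| φ | V | Common-factor share | Full-scale alpha = (15/14)(1 − 15/V) |
|---|---|---|---|
| 0 | 36.6 | 0.00 | 0.63 |
| 0.3 | 52.8 | 24.3/52.8 = 0.46 | 0.77 |
| 0.6 | 69.0 | 48.6/69.0 = 0.70 | 0.84 |

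Correlated factors strengthen the total; they do not rule it out.

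**3. The 0.60 check.** Varimax factors are uncorrelated by construction, so I read the check as applying to subscale sums. Their correlation is r = φ(kl)² / [k + k(k−1)l²], which is φ times the subscale reliability. With k = 8, l = 0.65 and φ = 0.6:

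- (8 × 0.65)² = 27.04
- 8 + 56 × 0.4225 = 31.66
- r = 0.6 × 27.04/31.66 = 0.51, below 0.60

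The limit is reached at φ = 0.60/0.854 = 0.70. Over 4 to 8 items per factor and loadings of 0.6 or 0.7, φ = 0.6 gives r between 0.42 and 0.53, so it passes in each case.

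**4. Eigenvalue >1.** Simulation with N = 300, 5-category items, three true factors correlated 0.4 and 300 replicates. Entries are mean numbers of factors retained.

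| Items | Loading | Full correlation matrix | Reduced (principal-factor) matrix | Parallel analysis |
|---|---|---|---|---|
| 15 | 0.5 | 3.9 | 1.0 | 2.9 |
| 15 | 0.6 | 3.0 | 1.8 | 3.0 |
| 30 | 0.5 | 8.1 | 3.0 | 3.0 |
| 30 | 0.6 | 4.8 | 3.0 | 3.0 |
| 45 | 0.5 | 12.8 | 3.0 | 3.0 |
| 45 | 0.6 | 8.2 | 3.0 | 3.0 |
| 60 | 0.5 | 17.7 | 3.0 | 3.0 |
| 60 | 0.6 | 12.2 | 3.0 | 3.0 |

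The rule over-extracts on the full matrix with long pools, under-extracts on the reduced matrix with a short pool, and is about right elsewhere. The article's gloss, that a retained factor explains more than one item, fits the full-matrix version, but the extraction method is not stated.

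**The case against.** The strongest reply is that rotation hardly changes the questionnaire. In a simulation at N = 300 (3 factors of 5 or 10 items, loadings 0.5 to 0.7, φ from 0.3 to 0.6, three factors kept, simple structure, 100 replicates), varimax and promax agreed on keeping or dropping 98-100% of items. They agreed on factor assignment for at least 99.9%. Varimax cross-loadings of 0.40 or more affected at most 0.1% of items. This stands under simple structure, and it limits the practical harm from rotation alone. Varimax is also conditional, and a condensed article may leave the step after a failed independence check to the full plan.

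A reader might infer four stronger things that the article does not support:

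- *The confirmatory model will be orthogonal and will misfit.* External validity assessment and Cross-cultural validation specify structural equation modeling and never fix factor covariances at zero. The listed fit indices could also expose such misfit.
- *Eigenvalue >1 will over-extract.* That depends on the matrix, item count and loadings, as the table shows.
- *The AUROC is compromised.* AUROC needs only a score that ranks patients, and a sum of weakly related facets can serve as an index.
- *The factor model contradicts the single score.* The sum can always be computed. The issue is whether it may be read as one construct, and the inter-item floor of 0.30 would flag wholly unrelated dimensions if applied across the scale.

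None of this makes the stated premise correct or gives the retention rule a second check.

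**Conclusion.** The point holds in limited form. The rationale for orthogonal rotation is wrong as a matter of algebra, with no assumption needed, and it is the only reason given for accepting poorer fit. The 0.60 check can pass factors truly correlated at 0.6 (subscale r about 0.51 at 8 items per factor and loading 0.65; 0.42 to 0.53 over the other settings tried).

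As a separate matter, eigenvalue >1 as sole rule is unreliable at N = 300. With three true factors and loading 0.6 it kept about 5 to 12 on the full matrix with 30-60 items, more at loading 0.5, and 1.8 on the reduced matrix with 15 items. These sizes rest on assumed item counts, equal loadings and simple structure.

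No planned result has been shown to change through rotation alone. The case for amending is that the stated reason is incorrect and both rules can be improved almost without cost.

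**What to change.** 1. Delete the statement that a global score is unavailable after oblique rotation.
2. Use an oblique rotation (for example promax) by default and report the factor correlations. Keep varimax only if they are all small, for example below 0.3; that cutoff is a suggestion.
3. Choose the number of factors by parallel analysis, with eigenvalue >1 as a secondary check, and state the extraction method so that the check has a definite meaning.
4. In the confirmatory analysis of the 364-patient cohort, let the factors correlate, and support the total score there, for example by a second-order or bifactor model where identifiable. With exactly three factors, an unconstrained second-order model cannot be tested against the correlated-factor model, so constraints or another argument would be needed.

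The cost is a few lines of text and code, with no new data. The one downside is that factor correlations must be reported and interpreted.
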